## Methods and analyses

### Study setting

This study is a randomized controlled, pragmatic single-center, parallel-group, 1:1 superiority trial. Our goal is to compare the effect of HTO and UKA in patients with late-stage medial knee OA. The study will take place in Helsinki University Hospital. Approximately 50 UKAs and 50 HTOs are performed in our hospital every year.

### Eligibility criteria

Orthopedic surgeons identify potential study participants from the referrals to outpatient clinics. Patients are scheduled for an outpatient visit to a surgeon member of the study group. Patients aged between 45 and 65 years with primary medial unicompartmental knee OA (Kellgren-Lawrence [KL] III–IV) [17] with varus deformity of 4 degrees or more can participate in the study. The patients are diagnosed according to clinical and radiologic examinations including MRI, weight-bearing knee, and mechanical axis radiographs. The patients meeting the inclusion criteria are asked to participate in the study. Written information and a consent form are given to the patient at the outpatient clinic. If the patient is willing to participate in the trial, they are scheduled for an appointment to the outpatient clinic once more for randomization and baseline measures. The detailed inclusion and exclusion criteria are shown in Table 1.

**Table 1 Tab1:** Inclusion and exclusion criteria used in the randomized controlled trial

**Inclusion criteria**
1. Symptomatic (more than 6 months) tibiofemoral medial joint arthrosis not responding to conservative treatment
2. Range of motion in clinical exam: extension 5° or less, flexion 120° or more
3. KL grade III–IV arthrosis in the medial compartment of the tibiofemoral joint
4. Modified Outerbridge grade III–IV arthrosis in MRI [18]
5. Varus alignment in mechanical axis ≥ 4°
6. Medial proximal tibial angle (MPTA) < 90°
7. Patient accepts the treatment options: HTO or UKA
8. Age 45–65 years
**Exclusion criteria**
1. Arthrosis in the lateral compartment of the tibiofemoral joint more than Modified Outerbridge classification grade I in MRI
2. Arthroscopic arthrosis more than grade I (Modified Outerbridge classification) in the lateral TF joint and/or meniscus tear or previous partial resection of meniscus
3. Instability due to ACL, PCL, MCL, or LCL insufficiency
4. Post-traumatic arthrosis
5. Inflammatory arthritis
6. Significantly impaired ability to co-operate for any reason (substance abuse, mental disorder, dementia)
7. Malignancy
8. Insulin-dependent diabetes
9. Previous surgery for instability of the knee joint (patellar instability, cruciate ligaments, MCL or LCL surgery)
10. Obesity (BMI > 35)
11. Unable to speak or read fluently either Finnish or Swedish (due to language used in data forms)
12. Contraindication for MRI

### Interventions

After recruitment, the patients are scheduled an appointment with a physical therapist and an individual training program is introduced. Patients are randomized to either HTO or UKA in 1:1 ratio. If the patients’ symptoms are reduced markedly before the operative treatment (1–4 months post randomization) a possibility for drop-out is offered. Both UKA and HTO operations are performed by experienced surgeons with at least 50 operations of UKA or HTO in total.

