### Outcomes

The outcomes of this study consist of objective and patient-reported outcomes. The outcomes will be collected at randomization, preoperative visit, and postoperatively 3, 6, and 12 months. We will follow up the participants thereafter at 2, 5, and 10 years via letter survey.

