**Table 2 Tab2:**
[figure not shown]
Participant timeline of the trial

After the surgery, the days spent in the hospital will be recorded to follow the early recovery. Early readmissions within 90 days after surgery for any reason are reported for the analysis of possible complications. See safety considerations for the list of complications monitored.

The OA progression is monitored at the follow-up visits using radiographs of the knee at 3, 6, and 12 months after surgery, and the mechanical axis is re-evaluated at 12 months post-randomization. Patients not satisfied with the results of operative treatment (HTO or UKA) can be converted to TKA at any time during the follow-up.

For later determining the MCID of KOOS_5_ in this study, we will include an anchor question to the trial: “If you think about your pain level and daily activities this week, would it be acceptable that your knee would be like this for the rest of your life?”. The answer options are “Yes” or “No.” The proportion of patients reaching the Patient Acceptable Symptom State (PASS) be analyzed from the answers to this question.

We will use the Withings Move electronic watch as an activity tracker. The watches are given to patients right after randomization and the patients are asked to wear them for 24 h per day until the primary time-point of 12 months. The following data are recorded: ID number, date, time, number of steps per day, and sleeping hours. The watch is connected to a secured database and the data is wirelessly transferred and stored.

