**Primary outcome measure**
1. KOOS_5_ at 12 months postoperatively

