### Statistical analyses

We will conduct all primary and secondary analyses according to the intention-to-treat principle. The Consolidated Standards of Reporting Trials statement will be used in the reporting of the trial results [32].

We will conduct the primary comparison (KOOS_5_ composite score) between the study groups using a mixed-model repeated-measures analysis of variance (MMRM ANOVA) allowing possible data missingness. We will assume data missing at random. Study group and time of assessment will be used as fixed factors and patients will be used as random factors. We are using the model to quantify the treatment effect as the absolute difference between the groups in KOOS_5_ (mean and 95% confidence interval [CI]) and *p*-value at 12 months postoperatively. A two-sided *p*-value of 0.05 will be used to indicate statistical significance.

We will compare secondary outcomes using a similar model where applicable (e.g., KOOS subscales, pain-VAS, Lysholm, Oxford knee score, OARSI). Radiological classification (KL- classification) is used for covariate in post hoc analysis. For categorical response variables, we will analyze the effects using the generalized estimating equations model with the unstructured correlation structure. Secondary outcomes will be considered explanatory and/or exploratory. Thus, multiplicity is not considered a problem. We will report adverse events descriptively.

We plan to perform a sensitivity analysis according to as-treated principle where the patients are analyzed according to their definitive treatment method irrespective of the randomization.

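### Randomised patients who improve before surgery are offered drop-out, yet KOOS5 follow-up is counted from surgery, so the intention-to-treat analysis has no defined 12-month score for those never operated on

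*Protocol article*

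**What the plan says.** All points are in the protocol article.

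- **Interventions.** After recruitment, "the patients are scheduled an appointment with a physical therapist and an individual training program is introduced". The section then states: "Patients are randomized to either HTO or UKA in 1:1 ratio". It goes on to say that if a patient's "symptoms are reduced markedly before the operative treatment (1–4 months post randomization) a possibility for drop-out is offered". It gives no threshold for a marked reduction and does not say what follow-up applies to those who accept.
- **Allocation, Implementation and Blinding.** The envelope is opened once consent is given, so patients learn their arm at randomisation. They are not blinded.
- **Outcomes.** "The outcomes will be collected at randomization, preoperative visit, and postoperatively 3, 6, and 12 months".
- **Table 3.** The primary outcome is "KOOS_5_ at 12 months postoperatively". The Primary outcome measure section uses the same clock.
- **Statistical analyses.** "We will conduct all primary and secondary analyses according to the intention-to-treat principle". The primary comparison is a repeated-measures mixed model that gives the group difference at 12 months after surgery. On missing values: "We will assume data missing at random".

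**The concern.** The offer comes after randomisation, to patients who know which operation they drew, and is triggered by a change in symptoms. Symptoms are part of what KOOS5 measures. A patient who accepts and is never operated on has no surgery date, so the 3, 6 and 12 month visits have no starting point. Intention to treat needs a 12-month outcome for each randomised patient, or at least a defined time at which to seek one. The protocol supplies neither for these patients.

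Two things are at stake. First, the result may come to describe patients who were still symptomatic when their operation came due, rather than all those randomised, with fewer observed scores. Second, if the offer is taken up more often in one arm, the two groups with 12-month data are no longer comparable.

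This is a matter of trial conduct as well as analysis. If the questionnaires are never sent, no later analysis can recover the scores.

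**Working it through.** **1. When the 12-month score exists.** For an operated patient the 12-month KOOS5 falls 12 months after the surgery date. For a randomised patient who is never operated on, the defined assessments are randomisation and, if attended, the preoperative visit. The 3, 6 and 12 month assessments have no date.

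**2. What the mixed model can do.** The article does not say which assessments enter the model as outcomes.

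- If only postoperative scores do, the never-operated patient contributes nothing.
- If pre-surgery scores do as well, the patient contributes as randomised and the 12-month value is missing. Under missing at random it is inferred from patients with similar earlier scores who went on to have surgery. That is the score expected with surgery, not the score this patient would report.

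**3. Effect on the group difference.** Let d be the share of an arm that leaves, and g the number of points by which leavers would have scored above those who stay. The mean of all randomised patients is the stayers' mean plus d × g, so the stayers' mean is too low by d × g. The error in the difference between arms A and B has size (dA − dB) × g, against the arm that loses more. The protocol gives neither d nor g, so both are assumed:

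- 10% v 4%, g = 10: (0.10 − 0.04) × 10 = 0.6 points
- 20% v 5%, g = 15: (0.20 − 0.05) × 15 = 2.25 points
- equal shares, any g: 0 points

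A second set of assumptions checks this. Suppose 25% of each arm improve, improvers score g points above the others at 12 months, and only improvers leave. The improvers then add g × (0.25 − d)/(1 − d) to the mean of those left.

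- 5% v 15%, g = 10: 10 × 0.20/0.95 − 10 × 0.10/0.85 = 2.11 − 1.18 = 0.93
- 0% v 20%, g = 10: 10 × 0.25 − 10 × 0.05/0.80 = 2.50 − 0.625 = 1.88
- 0% v 20%, g = 20: 20 × 0.25 − 20 × 0.05/0.80 = 5.00 − 1.25 = 3.75

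These are errors in raw observed means. The planned model would alter them to the extent that earlier scores predict later ones.

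**4. Effect on power.** Inputs from Sample size: difference 10, SD 15, two-sided alpha 0.05, power 80%.

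- Plan's figure: n = 2 × (1.960 + 0.842)² × 15²/10² = 2 × 7.85 × 2.25 = 35.3, so 36 per group. This reproduces the stated 36. An exact t-test at 36 has 79.7% power.
- Room for losses: 50 − 36 = 14 patients per arm.
- The protocol's own 36% loss: 50 × 0.64 = 32 per arm, t-test power 74.7%.

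The article does not say whether the 36% already counts patients who take the offer. If it does, there is no further loss. If they come on top of it:

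| Extra departures (assumed) | n per arm | t-test power |
|---|---|---|
| 5% | 32 × 0.95 = 30.4 | 72.5% |
| 10% | 32 × 0.90 = 28.8 | 70.1% |
| 20% | 32 × 0.80 = 25.6 | 64.7% |

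How a 36% loss was turned into 50 per group is a separate question and does not affect this point.

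**The case against.** The other side has a good deal to say, and several stronger readings fail on it.

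- **A reader might infer that all follow-up hangs on surgery.** It does not: "the mechanical axis is re-evaluated at 12 months post-randomization", and the activity watch is worn from randomisation. The gap concerns KOOS5 and the primary comparison.
- **A reader might infer that improved patients cannot enter the analysis.** The text does not establish this. Scores at randomisation and at the preoperative visit could keep them in a model that allows missing values. Nor does Interventions say that follow-up stops for those who accept.
- **Missing at random may partly fit.** If improvement is recorded at the preoperative visit, missingness that depends on it is what the assumption covers. Doubt remains for patients who leave before that visit, and because the inferred score is that of operated patients.
- **A reader might take the Generalizability section as evidence that preference will make departures differ by arm.** That section concerns unwillingness to join the trial and answers it with the cohort of decliners. Inclusion criterion 7 admits only patients willing to have either operation.
- **Improvement itself should be balanced.** Before surgery both arms get the same physiotherapy appointment and training, and neither operation has happened. Only the decision to leave, taken with the allocation known, can differ.
- **Sensitivity analyses for missing data commonly sit in the analysis plan**, which is not shown. Their absence from the article is no fault.

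What the objection does not remove is that the article fixes a surgery-based clock for its primary outcome, provides for randomised patients who will have no surgery, and promises to analyse everyone as randomised. These three statements do not fit together.

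**Conclusion.** The point holds in this form: the drop-out offer and the postoperative timing of KOOS5 leave a randomised, never-operated patient with no defined 12-month primary score, which conflicts with the declared intention-to-treat analysis. At best the score is inferred from operated patients.

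Bias between the arms is conditional. With equal departures it is zero, and the cost is power and a narrower target population. With unequal departures it is about 0.6 to 2.3 points under the main assumptions and up to 3.75 under the most extreme case shown, against an MCID of 10. Every departure share and score advantage here is assumed. If patients who forgo surgery would score below those who stay, the sign reverses. The documents contain no evidence that departures will differ by arm; they show only that the decision is made with the allocation known and without a threshold. It would therefore go too far to say that the trial's result will be biased. The point should be put right because the remedy is cheap and the missing scores cannot be recovered later.

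**What to change.** Reconcile Interventions, Outcomes and Statistical analyses so that not having surgery does not mean leaving the trial. The decision about surgery itself can stay as the protocol has it. Three statements are enough:

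1. A randomised patient who does not have surgery is asked to stay in follow-up.
2. That patient is analysed in the arm to which he or she was randomised.
3. The 3, 6 and 12 month KOOS5 for such patients is timed from a defined date, such as the originally scheduled surgery date, which is recorded when it is set.

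Patients may still withdraw consent, and their 12-month scores would remain missing. The change should make them fewer.

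The cost is some protocol wording and a few more questionnaires. Patients without surgery dilute the contrast between the operations slightly, which intention to treat accepts. Trial status describes a trial that had not yet started at version 1.2, and Protocol amendments provides a route for changes.

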### Surgical technique

#### HTO — high tibial osteotomy (open wedge)

An open wedge HTO is a standard approach in our clinic and thus used as the surgical technique in this study. Weight-bearing mechanical axis radiograph is used to plan the desired correction. An arthroscopy of the knee is performed first to determine the degree of OA. Arthrosis of the lateral and medial TF joint is graded by the modified Outerbridge classification [18, 19]. Patients with lateral OA grade II or greater are excluded from the study at this point. Cruciate ligaments and menisci are also evaluated in the arthroscopy.

A medial high tibial open wedge osteotomy is performed using a diagonal incision just cranial to pes anserinus tendons or a medial longitudinal incision. Pes anserinus tendons are retracted distally and the superficial medial collateral ligament is exposed and incised at the level of the planned osteotomy. Two parallel K-wires are inserted under image intensifier to mark the osteotomy level. Patellar tendon is protected and a biplanar osteotomy line is created using an oscillating saw and osteotomes leaving the lateral cortex intact and the tibial tubercle to the distal side of the osteotomy. Thin osteotomes are used to open the osteotomy after sawing to achieve the desired correction (Fujisawa point) [20]. The osteotomy site is secured using a medial locking plate (TomoFix®, DePuy Synthes, Raynham, MA, USA). The wound is closed in a standard manner. Local infiltration analgesia is used for all patients. An elastic bandage is applied. Weight-bearing as tolerated is allowed immediately after the surgery.

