#### UKA — unicompartmental knee arthroplasty

Oxford® Partial Knee (Zimmer Biomet, Warsaw, IN, USA) arthroplasty (PKA) is performed from medial parapatellar arthrotomy without dislocating the patella. Tourniquet is used for every patient if no contraindications exist. Retropatellar fat pad is partially resected if necessary, to ensure adequate surgical visualization. The anterior cruciate ligament is inspected for possible ligament rupture and fibrillation, and lateral and patellofemoral joint compartments are inspected for possible cartilage damage. Patients with lateral OA grade II or greater are excluded from the study at this point. Grade of medial femoral and tibial cartilage loss is verified. All osteophytes are removed from the intercondylar notch, medial margin of the medial condyle, tibial plateau, and patella. PKA instrumentation and implantation are performed according to the cementless Oxford® PKA Microplasty® (Zimmer Biomet, Warsaw, IN, USA) instrumentation system technique. Local infiltration analgesia is used for all patients. The wound is closed in a standard manner. An elastic bandage is applied. Full weight-bearing is allowed immediately after the surgery [21].

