### Implementation

The recruitment is done by the surgeon member of the study. After receiving the written consent, the surgeon member opens the envelope, and the patient is then randomized to one of the study groups. A physical therapist does the baseline measures, and the patient receives a written guide for exercise therapy.

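### Randomised patients are removed from the study during surgery for lateral osteoarthritis, assessed differently in the two arms, which contradicts intention to treat and can bias the comparison

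*Protocol article*

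**What the plan says.** Randomisation takes place at the outpatient clinic. Under Implementation, once consent is signed, "the surgeon member opens the envelope, and the patient is then randomized to one of the study groups". The Interventions section dates surgery relative to that moment, in its remark on patients whose symptoms ease: "before the operative treatment (1–4 months post randomization) a possibility for drop-out is offered".

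In the HTO section, "An arthroscopy of the knee is performed first to determine the degree of OA". The lateral and medial joint is graded by the modified Outerbridge classification, and then: "Patients with lateral OA grade II or greater are excluded from the study at this point". The section adds: "Cruciate ligaments and menisci are also evaluated in the arthroscopy".

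In the UKA section, the operation "is performed from medial parapatellar arthrotomy without dislocating the patella". The lateral compartment is inspected for cartilage damage, and the same exclusion sentence follows word for word. No arthroscopy is described there.

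Table 1, exclusion criterion 2, reads: "Arthroscopic arthrosis more than grade I (Modified Outerbridge classification) in the lateral TF joint and/or meniscus tear or previous partial resection of meniscus". Criterion 1 separately excludes lateral disease above grade I on MRI.

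The Blinding section states that operating personnel cannot be blinded. The Statistical analyses section opens: "We will conduct all primary and secondary analyses according to the intention-to-treat principle". The only sensitivity analysis it names is as-treated.

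**The concern.** A randomised patient who is taken out of the study cannot be in an intention-to-treat analysis. The exclusion sentence speaks of the study, not of the operation, and nothing says that these patients are followed or analysed as randomised.

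Removing patients for a condition that existed before randomisation can be harmless if it is found in the same way in both arms by someone unaware of the allocation. Neither condition is met here. The access and the described assessment differ by arm, and the operating team knows the arm. If one method finds more lateral disease than the other, the arms that remain are no longer the groups that randomisation formed. The patients removed may also differ in prognosis for KOOS5.

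**Working it through.** **1. Order of events.** Consent, then envelope, then 1–4 months, then surgery, then possible exclusion. The exclusion is after randomisation in both arms.

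**2. What can be checked before allocation.** Criterion 1 (MRI) can be. The meniscal parts of criterion 2 may be, since a previous resection is known from history and a tear may show on the MRI. The arthroscopic part of criterion 2 cannot be, because the only arthroscopy described is the first step of the HTO operation. The UKA section applies the same threshold (above grade I is grade II or more) by a different route.

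**3. Whether the planned analyses repair it.** The mixed model assumes data missing at random, with group and time as fixed factors. Removal depends on the intra-operative lateral grade, which is not in the model. The as-treated analysis reassigns patients who are still in the study and does not recover those removed. The ineligible cohort (Secondary cohort study) needs consent and is analysed separately from the trial.

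**4. The plan's own figure.** Difference 10, SD 15, two-sided 5%, 80% power: n = 2 × (1.960 + 0.842)² × 15² / 10² = 35.3, so 36 per group. This reproduces the stated 36. With 50 per arm, 36 remain only if total loss, including removals at surgery, is at most 1 − 36/50 = 28%. With no other loss, removing 10% leaves 45 per arm (87.9% power by t-test) and 20% leaves 40 (83.8%).

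**5. Size of a possible bias.** The documents give no rates, so every input here is an assumption. Let q be the share of randomised patients with lateral grade II or more at surgery, s the share of these detected in an arm, and D their shortfall in KOOS5 at 12 months, the same in both arms. The true treatment difference is 0. The mean of the patients who remain in an arm is shifted by −D × q(1 − s)/(1 − qs), and the bias is the HTO shift minus the UKA shift.

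- q = 10%, D = 10, detection 95% (HTO) v 50% (UKA): −10 × 0.10 × 0.05/0.905 = −0.06, and −10 × 0.10 × 0.50/0.95 = −0.53. Bias 0.47.
- q = 20%, D = 20, same detection: −20 × 0.20 × 0.05/0.81 = −0.25, and −20 × 0.20 × 0.50/0.90 = −2.22. Bias 1.98.

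| q | D | Detection HTO v UKA | Bias (points) | Type I error |
|---|---|---|---|---|
| any | any | equal | 0 | 5.0% |
| 5% | 5 | 95% v 50% | 0.12 | 5.0% |
| 10% | 10 | 90% v 60% | 0.32 | 5.1% |
| 10% | 10 | 95% v 50% | 0.47 | 5.3% |
| 20% | 20 | 95% v 50% | 1.98 | 9.3% |
| 20% | 20 | 100% v 0% (extreme) | 4.0 | 24.2% |

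A positive value favours HTO. Swapping the two detection rates reverses the sign.

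**The case against.** The best defence has four parts.

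- **MRI screening.** MRI already removes lateral disease above grade I in both arms before randomisation. Only patients whose MRI looked acceptable but whose joint did not can be removed at surgery. This stands: the numbers should be small, and the higher prevalences in the table may be too pessimistic.
- **Same threshold.** Both sections use the same threshold, and both teams see the joint directly. The documents do not say that arthrotomy detects less than arthroscopy. This also stands, so unequal detection is a possibility and not an established fact.
- **Size.** The bias in the moderate scenarios is below the standard error of the difference at 50 per arm, 15 × √(2/50) = 3.0 points. True, but bias does not average out as sampling error does, and here it can be avoided at little cost.
- **Left to the SAP.** Analysis-set rules are often left to a SAP, which is not shown. That would answer a silent protocol. This one states a rule that conflicts with its own analysis principle.

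A reader might infer more than the text supports. One might conclude that the rule favours HTO by a known amount, but no detection rate or outcome deficit is given. One might say that criterion 2 can operate only in the HTO arm, but this holds only for its arthroscopic part. One might also read the meniscal evaluation at arthroscopy as a further removal rule confined to HTO, but the exclusion sentence in both arms names lateral osteoarthritis only.

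**Conclusion.** The conflict is certain: two sections remove randomised patients from the study, and a third promises intention to treat for every primary and secondary analysis. The arthroscopic part of criterion 2 adds to it, because it makes an eligibility condition of something first seen after allocation. That the rule can bias the comparison is also clear, given unblinded judgement and different assessment by arm. How much, and in which direction, cannot be determined from the documents. The illustrative 0.5 to 2 points rests wholly on the assumed detection of 95% v 50%, prevalence of 10–20% and deficit of 10–20 points, and it falls to zero if detection is equal. The loss of power is secondary: even 20% removed leaves 40 per arm if nobody else is lost. The point should be settled before recruitment, because outcomes of patients who are not followed cannot be recovered later.

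**What to change.** Reconcile Table 1, the two technique sections and the Statistical analyses section.

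- In both technique sections, replace the exclusion sentence with: the lateral finding is recorded; the patient remains in follow-up on the normal schedule and is analysed in the randomised group, whatever operation is done.
- State that the arthroscopic part of criterion 2 does not remove a randomised patient from the analysis. Leave the criteria that can be checked before randomisation (MRI, meniscal history) as they are; there is no need to delete criterion 2 as a whole.
- Report the number of such findings by arm, and leave these patients out only in a supportive analysis.

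The cost is a change of wording, follow-up of a few more patients, and slight dilution of the contrast if some receive another operation. What the surgeon does on finding lateral disease is a clinical matter that this change does not address.
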